### Recruitment, consent, and allocation to interventions

Participants will be recruited by local advertisements and recruitment talks in the San Francisco Bay Area, online dementia caregiving groups, and by accessing an established research registry database. Recruitment is planned to continue until 40 eligible participants are enrolled (20 per intervention arm), and the approximate recruitment period is 2 months. Participants will not receive financial compensation for taking part in the study, and there will be no inducements for completing interventions. Participants deemed suitable for recruitment, will be contacted *via* email or phone with an opportunity to participate in additional eligibility screening, and to complete an online screening questionnaire to confirm eligibility. A follow-up email will include a review of study details (e.g., start date, expectations).

All screening and recruitment conversations will be completed by research personnel trained in the ethical conduct of human subjects’ research. Informed written consent will be obtained *via* interview with a trained examiner (*via* Zoom), during which the study will be clearly explained in detail, and caregivers will be able to ask questions prior to enrollment. Caregivers will also be informed that they can drop out of the study at any time. After this conversation, those agreeing to participate will be asked to formally consent to study participation. Due to current pandemic restrictions, DocuSign will be used to obtain participants’ consent signatures electronically. The amount of time expected for this consenting process is 20 min.

Next, for the baseline assessment part of the study (T0, 0 months), enrolled participants will be scheduled to participate in a 10-min semi-structured online interview *via* Zoom (see Supplementary material) and will complete a set of online surveys and performance tasks *via* Qualtrics. Those evaluations are designed to minimize possible subject fatigue, stress, and boredom. Breaks from testing will be allowed, and testing sessions may also be broken into multiple sessions. After all participants have completed enrollment and baseline assessment, they will be randomized to one of the two study arms and will then be informed *via* email of the group to which they have been assigned (see Figure 1; Table 1).

**Figure 1 fig1:**
[figure not shown]
Planned flow of participants.

**Table 1 tab1:** Schedule of enrolment, interventions, and assessments.

Timepoint	Study period				
	Enrolment	Randomization	Intervention		Close-out
	*t_−1_*	*t_0_*	*t_1_*	*t_2_*	*t_x_*
Enrolment					
Eligibility screen	X				
Informed consent	X				
Allocation		X			
Interventions					
*MBSR adapted program*					
*GARDEN*					
Assessments					
*Primary outcome*		X	X	X	
*Secondary outcome*		X	X	X	
*Tertiary outcome*		X	X	X	

Randomization with 1:1 allocation ratio to one of the two arms will be conducted by a study investigator with no participant contact. Participants will be randomly allocated *via* a computerized random number sequence, generated *via* the R software (Team, 2014). Allocation will remain concealed from the study staff and participants during screening until randomization is completed.

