### Sample size calculation

Because this is a novel study and there are no published effect sizes for the impact of this mindfulness-based intervention on our various outcomes, this study will establish preliminary effect sizes for all measures. Due to the highly interpersonal nature of the mindfulness intervention, enrolling more than 20 participants per arm was impractical; however, considering expected attrition, this sample size will only be powered to detect large between-group effect sizes (i.e., 80% power to detect *r* > =0.70; 25% power to detect *r* > = 0.50).

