### Interventions

#### Mindfulness-based intervention (interactive program)

Caregivers allocated to this experiential group will take part in an adapted mindfulness-based stress reduction (MBSR) program, formatted as a live class led by two certified MBSR instructors *via* Zoom, where they practice and receive feedback on mindfulness skills. To maintain group cohesiveness, while maximizing study enrollment, two separate classes of 10 caregivers each will be conducted concurrently. Recognizing that caregivers report having restricted time availability, this mindfulness-based intervention will have shortened sessions (1.5 h each) compared to the traditional MBSR 2.5 h-sessions, to better accommodate caregivers’ needs. MBSR adaptations with abbreviated weekly sessions and daily time commitment have been shown to still render significant decreases in perceived stress (Klatt et al., 2008; Carmody et al., 2009; Hoppes et al., 2012). Caregivers will be trained in meditation practices, learn about mindfulness, and stress theory, and have group discussions covering topics such as dementia caregiving challenges, and grief in dementia caregiving. The program curriculum (see Table 2) extends over a period of 8 weeks, where participants are encouraged to complete home practices and review reading material between live sessions.

**Table 2 tab2:** Weekly MBSR adapted course content.

	Topic	Content
Session 1	Introduction to mindfulness; Finding Stillness	Introducing caregivers to the notion of mindfulness as a way of being, exploring their needs and expectations from their participation, setting the group environment, and defining the term of “awareness” as a fundamental pillar of mindfulness
Session 2	Perception and its relation to stress; Perception and Perspective Taking	Highlighting the importance of commitment to practices, exploring the notion of a “non-judgmental” attitude toward the participants’ handling of practice as well as challenges, introducing the exploration of different angles of perception and perspective taking, and investigating the “habits & barriers” set by our automatic responses

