### Data analysis plan

The study will use mixed methods, integrating quantitative and qualitative strategies, making no assumptions about linear relationships between quantitative and qualitative data/findings (DePoy and Gitlin, 1994). These two strategies will be employed as different ways of exploring and understanding the theme in question, i.e., mindfulness and caregiver wellbeing.

Regarding quantitative measures we will first identify factors that are confounders between the two intervention groups, which may include socio-demographics, relationship to care recipients, healthcare access, socioemotional support, dementia patient diagnosis, engagement in intervention, relationship quality with facilitator, hours (weekly) spent with the person with dementia. Any variables showing significant group differences will then be considered confounds and included in the main statistical analyses. We will also check for missing data and signs of systematic response bias in self-reported responses. The main analysis will evaluate the effect of treatment group x time (t0, t1, t2). All participant outcome measures (domains: relational well-being, psychological well-being, dementia patient’s lifestyle changes), will be analyzed using generalized linear mixed models. Models will treat treatment and time points (including their interaction) as fixed effects and caregivers as random effects. We will look for a main treatment effect, a main time effect, and an interaction effect of treatment by time. All hypotheses will be individually evaluated at a nominal *p*-value of 0.05.

Semi-structured interviews will be analyzed using thematic analysis. First, grounded theory’s open coding stage will be employed, followed by axial coding and analyses (Spradley, 1979; Charmaz, 2006). We will identify meaningful themes and conceptualize our findings in relation to existing mindfulness theories and stress reactivity research. Because the first two authors are mindfulness teachers who have worked extensively with older adults, including dementia caregivers, qualitative data will be analyzed separately and jointly by the first two authors. Final synthesis of analyzed data will be obtained through continuous discussions among the research team until consensus is reached.

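### Baseline imbalance in a 40-person trial is left to a significance screen that misses most of it, although every baseline is known before allocation

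*Protocol article*

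**What the plan says.** Under Recruitment, consent, and allocation to interventions, the timing is explicit: "After all participants have completed enrollment and baseline assessment, they will be randomized to one of the two study arms". The same section sets the method. The ratio is 1:1, run by an investigator without participant contact, and "Participants will be randomly allocated *via* a computerized random number sequence", produced in R. Procedures to reduce bias repeats this. Neither place mentions stratification, minimisation or any other balancing, and neither calls the sequence simple or unrestricted.

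Arm size is addressed in three places. The recruitment section gives a target of 40, 20 in each arm. Sample size calculation says that "enrolling more than 20 participants per arm was impractical". The description of the mindfulness programme says that "two separate classes of 10 caregivers each will be conducted concurrently".

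The Data analysis plan gives the rule for imbalance: "Any variables showing significant group differences will then be considered confounds and included in the main statistical analyses". Its candidate list mixes baseline characteristics (socio-demographics, relationship to the care recipient, healthcare access, socioemotional support, the patient's diagnosis, weekly hours together) with two variables that arise only after allocation: engagement in the intervention and relationship quality with the facilitator. The main analysis is a mixed model for treatment, time (T0, T1, T2) and their interaction, with caregiver as a random effect. The plan says it will look at the main treatment effect as well as the interaction.

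**The concern.** The authors name the factors they regard as possible confounders. The Introduction reports greater burden, distress and depressive symptoms in caregivers of people with frontotemporal dementia than in caregivers of people with Alzheimer's disease, and the Design section admits all categories of dementia. All these data are in hand when the list is run, which is the easiest setting for balancing by design. The article describes no such step and relies on a significance test instead.

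That test is a poor selector for three reasons. After proper randomization it tests a null hypothesis known to be true, so it picks covariates by chance and not by prognostic strength. At this sample size it lets moderate imbalances through. And if engagement or the relationship with the facilitator passes the screen, the model adjusts for something the intervention may have changed, which can remove part of the effect being estimated. The study exists to produce preliminary effect sizes, so the quality of each estimate matters more than any single p-value.

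**Working it through.** **Inputs.** 20 per arm and allocation after all baselines (recruitment section); 80% retention to T1 (Strategies for improving adherence); the screening rule and nominal 0.05 (Data analysis plan). The sidedness and level of the screen are not stated; I assume two-sided 5%. The plan gives no figure of its own on imbalance to reproduce.

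**1. What the screen can see.** The standard error of a standardized difference is √(2/20) = 0.316. The threshold is t(0.975, 38) × 0.316 = 2.024 × 0.316 = 0.64 SD. At a 10% level it would be 1.686 × 0.316 = 0.53 SD. If the screen is run on the 16 per arm implied by 80% retention, it rises to 2.042 × √(2/16) = 2.042 × 0.354 = 0.72 SD.

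**2. How often imbalance arises, arms fixed at 20/20, no balancing.**
- Continuous factor, normal approximation: P(|difference| > 0.3 SD) = 2 × P(Z > 0.949) = 34%; P(> 0.5 SD) = 2 × P(Z > 1.581) = 11.4%.
- At least one of five independent factors above 0.5 SD: 1 − (1 − 0.114)^5 = 45%.
- Binary factor, hypergeometric: a gap of 20 percentage points or more in 24%, 30% and 34% of allocations if 8, 12 or 20 of the 40 carry it (assumed prevalences of 20%, 30% and 50%; the documents give none).

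**3. How much of it goes uncorrected.** The screen flags 5% of allocations per factor. Of imbalances above 0.3 SD, (34.3 − 5)/34.3 = 85% are not flagged. Above 0.5 SD, (11.4 − 5)/11.4 = 56% are not flagged (59% if the 0.5 SD tail is taken from the t distribution, 12.2%). Binary example: 13/20 against 7/20, a 30-point gap, gives an uncorrected chi-square of 40 × (13×13 − 7×7)²/20⁴ = 3.6, p = 0.058, so no adjustment.

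**4. What reaches the estimates.** Let a factor X have slope b_t on the outcome at time t (outcome SDs per SD of X), and let the arms differ by Δ on X.
- Comparison of levels: shift = b_t × Δ. With an assumed slope of 0.5 and Δ = 0.5 SD, this is 0.25 SD.
- Treatment-by-time contrast: shift = (b_1 − b_0) × Δ. If the slope is the same at both times and data are complete, this is zero. If it moves from an assumed 0.5 to 0.3, it is −0.2 × 0.5 = −0.10 SD.
- The outcome's own baseline: with correlation ρ between T0 and T1 and equal SDs, a baseline gap of Δ shifts the change contrast by (ρ − 1) × Δ. For Δ = 0.5 and assumed ρ of 0.5 to 0.8, this is −0.25 to −0.10 SD.

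**5. Arm sizes, only if the sequence were simple.** Binomial(40, 0.5): exactly 20/20 has probability 12.5%, and more than 20 in the mindfulness arm has (1 − 0.125)/2 = 43.7%. A 24/16 split keeps 4 × 24 × 16/40² = 96% of the efficiency of 20/20.

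**The case against.** A reader might infer that the trial uses unrestricted randomization and leaves arm sizes to chance. The article does not say so. A 1:1 ratio, 20 per arm, a stated ceiling of 20 and two classes of 10 all fit a list of 20 and 20 put in random order, and the full protocol may specify exactly that. The 44% figure is therefore a reason to state the method, not evidence of a fault. Nor would power be the issue, given step 5.

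A reader might also infer that a 0.5 SD imbalance biases the main result by 0.25 SD. That holds for a comparison of levels. The main analysis is the treatment-by-time effect, and there stable additive effects of diagnosis or relationship are already in the T0 value and cancel with complete data. This objection stands and limits the harm to the three routes in the verdict.

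Unstratified randomization is valid, chance imbalance is part of sampling error, and this is a declared exploratory pilot. All true, and an article may leave details of restriction to a fuller document. But the covariate rule is not an omission: it is written out, and it is the part that works badly. Finally, the Introduction's contrast by diagnosis comes without effect sizes and does not concern change under intervention, so it supports naming diagnosis as a covariate but gives no size of harm.

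**Conclusion.** The point holds in a limited form. The stated rule for handling imbalance should be replaced, and the batch allocation offers an unused chance to balance by design. At 20 per arm the screen sees only differences of about 0.64 SD or more, while differences above 0.5 SD on a given continuous factor occur in about 11% of allocations and more than half of those pass unadjusted. The consequences reach (a) the separately listed main treatment effect, (b) the treatment-by-time contrast for factors that predict change, and (c) the same contrast through regression to the mean when the outcome differs at baseline. The documents do not allow (b) and (c) to be sized; the 0.10 to 0.25 SD values above are illustrations. Admitting post-allocation variables is a fault whatever the degree of imbalance.

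The figures assume a two-sided 5% screen, arms fixed at 20/20 and, for the five-factor figure, independent factors.

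**What to change.** **Analysis, possible whether or not allocation has taken place, provided it is settled before outcome data are examined.** Replace the significance screen in the Data analysis plan with two or three named baseline covariates in every model, each allowed to interact with time: for example the care recipient's diagnosis group, relationship to the care recipient and, for the relational outcome, baseline FCI-MS. Where FCI-MS is itself the outcome, use T0 as the covariate and model T1 and T2, so that the same value is not on both sides. Remove engagement, relationship with the facilitator and the amount of the programme completed from the adjustment set; they can be reported descriptively.

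**Allocation, if it has not yet occurred.** Use covariate-constrained randomization on the same factors: generate 20/20 allocations in R, keep those that meet a preset balance criterion, and draw one at random. This is preferable to stratified blocks, because three binary factors give 8 cells averaging 5 people, and sparse or odd cells would not guarantee 20/20. The investigator without participant contact can run it as planned.

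**Reporting.** State in one sentence that the list is fixed at 20/20, since a simple sequence would exceed the 20 mindfulness places about 44% of the time.

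**Cost.** A few lines of code, two or three protocol sentences and a few model degrees of freedom. No extra participants or visits.

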### Interventions

#### Mindfulness-based intervention (interactive program)

Caregivers allocated to this experiential group will take part in an adapted mindfulness-based stress reduction (MBSR) program, formatted as a live class led by two certified MBSR instructors *via* Zoom, where they practice and receive feedback on mindfulness skills. To maintain group cohesiveness, while maximizing study enrollment, two separate classes of 10 caregivers each will be conducted concurrently. Recognizing that caregivers report having restricted time availability, this mindfulness-based intervention will have shortened sessions (1.5 h each) compared to the traditional MBSR 2.5 h-sessions, to better accommodate caregivers’ needs. MBSR adaptations with abbreviated weekly sessions and daily time commitment have been shown to still render significant decreases in perceived stress (Klatt et al., 2008; Carmody et al., 2009; Hoppes et al., 2012). Caregivers will be trained in meditation practices, learn about mindfulness, and stress theory, and have group discussions covering topics such as dementia caregiving challenges, and grief in dementia caregiving. The program curriculum (see Table 2) extends over a period of 8 weeks, where participants are encouraged to complete home practices and review reading material between live sessions.

**Table 2 tab2:** Weekly MBSR adapted course content.

	Topic	Content
Session 1	Introduction to mindfulness; Finding Stillness	Introducing caregivers to the notion of mindfulness as a way of being, exploring their needs and expectations from their participation, setting the group environment, and defining the term of “awareness” as a fundamental pillar of mindfulness
Session 2	Perception and its relation to stress; Perception and Perspective Taking	Highlighting the importance of commitment to practices, exploring the notion of a “non-judgmental” attitude toward the participants’ handling of practice as well as challenges, introducing the exploration of different angles of perception and perspective taking, and investigating the “habits & barriers” set by our automatic responses
Session 3	The power of being present; There is Pleasure & Power in Being Present	Expanding the awareness toward the present moment with a “no striving” attitude, introducing the concept of “power of choice” to caregivers and their challenges, deepening of mindfulness practices, and encouraging caregivers to expand on their awareness of noticing and appreciating pleasant moments in any experience
Session 4	The relation between mindfulness and stress; How Does Mindfulness Relate to Stress?	Exploring the relationship between stress reactivity, automaticity, and mindfulness, investigating maladaptive coping mechanisms stemming from stressful situations, modelling “acceptance” in caregivers’ experiences, expanding on the concept of grief in caregiving, and exploring the physiological territory of stress
Session 5	The difference between responding and reacting; Responding vs. Reacting	Introducing the concept of mindfully responding rather than automatically reacting to stress, considering the role of reactivity and its effects on health and suffering, discussing the role of feelings (e.g., anger, sadness, and grief), understanding the importance of being able to express feelings effectively, practicing acceptance, and assessing commitment and practicing in the middle of the intervention
Session 6	Learning about stressful communications; Stressful Communications	Shifting and extending focus from practicing intrapersonal to interpersonal mindfulness, learning to maintain inner balance while interacting, being aware of feelings, sensations, and thoughts while interacting with others, especially under conditions of acute or chronic stress, introducing the attitude of “letting-it-be & letting-it-go,” and exploring difficult communications in dementia caregiving
Retreat	Mindfulness Day/Silent Retreat	Three (3)-hour silent retreat. Extending mindfulness practices in a variety of approaches, reinforcing and deepening of mindfulness practices, while staying in silence for the duration of the retreat
Session 7	Learning and exploring self-resilience; Cultivating self-resilience	Expanding practices to daily caregiving life, introducing the fundamental mindfulness aspect of “trust” into daily life and caregivers’ challenges, cultivating psychological self-resilience, exploring the territory of self-compassion and self-reflection
Session 8	Continued practice, Wrap-up; Endings are New Beginnings	Reflecting on experiences of participations, cultivating the attitudes of “gratitude & generosity,” exploring the possibility of writing a personal letter for a recommitment to the individual practices in the future, overviewing of all practices, and unwrapping the dementia gifts for the mindful caregiver

The intervention is based on the manual of MBSR (Santorelli et al., 2020) and has been customized to the needs of dementia caregivers. To tailor the program, MBSR facilitators executed an in-depth literature search about challenges associated to dementia caregiving (Manteau-Rao and Barrows, 2016) and modified course material to explicitly integrate dementia caregiving concerns and experiences into the educational and practical material wherever relevant. Drawing from previously established mindfulness-based dementia care approaches, the focus of our mindfulness-based intervention is the development of mindfulness practice, sustaining attitudinal changes, reducing stress, and enhancing interactions throughout the caregiving journey (Dioquino et al., 2016). The structure of every session includes (1) educational input and scientific background to course elements, (2) mindfulness practices, (3) reflection of one’s practice and experience, (4) role plays or group exercises/discussions, and (5) home assignment discussions.

#### Active control group (self-guided program)

Caregivers allocated to this study arm will be assigned to a self-guided, online, weekly program that specifically targets positive emotion (Cheung et al., 2018; Addington et al., 2019; Moskowitz et al., 2019). The material aims to cultivate skills such as positive reappraisal, gratitude, self-compassion, and setting manageable goals. The program consists of skills introduced gradually over a 6-week period that caregivers will learn about and practice independently. Caregivers will also be asked to complete a daily questionnaire recording their feelings. To better mimic the structure of the active MBSR arm, which is in-person weekly, participants in this control arm will also be asked to participate in two online, interactive group discussions with other caregivers (*via* Zoom) at Week 4 and Week 8, facilitated by the study’s research director. This component will provide a space for caregivers to interact in person with others and discuss stressful experiences and application of skills learned to daily caregiving challenges. Study personnel are able to monitor the degree of completion of each module and will communicate with any caregiver who seems to be falling behind or otherwise not completing the work.

